**Methods and analysis:**

We will conduct the Platelet-Rich plasma Injection Management for Ankle OA study: a multicentre, randomised, placebo-controlled trial. One hundred patients suffering from ankle OA will be randomised into two treatment groups: PRP injection or placebo (saline) injection. Both groups will receive two injections of PRP or placebo at an interval of 6 weeks. Primary outcome is the American Orthopaedic Foot and Ankle Society score at 26 weeks. Secondary outcomes determined at several follow-up moments up to 5 years, include Ankle Osteoarthritis Score, Foot and Ankle Outcome Score, pain subscale of (0–40), Visual Analogue Scale score (0–100), Ankle Activity Score (0–10), subjective patient satisfaction Short Form Health Survey-36, Global Attainment Scaling and the EuroQol-5 dimensions-3 levels utility score. A cost-effectiveness analysis will be performed at 1 year.

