### Randomisation, blinding and treatment allocation

We will include patients at the centre of their first outpatient clinic appointment. For each patient the coordinating researcher will prepare a syringe with PRP and a syringe with placebo (isotonic saline: 0.9% sodium chloride). A Good Clinical Practice (GCP) approved data management system (Castor EDC, based in Amsterdam, the Netherlands) will be used to perform a computer-generated block randomisation scheme with patients stratified to centre with a variable block size of 2, 4 or 6. This procedure will ensure treatment allocation concealment. The coordinating researcher, treating physician and patient all remain blinded to the allocated intervention. An independent researcher from the coordinating location will have access to the randomisation result and the allocated intervention. This will be relayed to a GCP-certified research assistant at the centre. The research assistant then selects one of the two syringes based on the allocated intervention and blinds the syringe with a covering sheath, ensuring concealment of the content of the syringe. The patients, treating physicians and coordinating researcher will all be blinded to the allocation of the intervention and to the contents of the syringe. The success of blinding will be assessed by asking patients which injection they think they have received just after the injection procedure, this will then be registered accordingly.

After the 26 weeks follow-up of the last patient in the study, the principal investigator and coordinating researcher will be unblinded only after the analysis of the primary outcome. The patients will remain blinded to the therapy until the 52 weeks follow-up (online supplementary appendix 1) of the last patient in the study.

10.1136/bmjopen-2019-030961.supp1Supplementary data

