### Sample size

Based on previous and ongoing studies, the study protocol of the RCT is designed to detect a difference of 12 points (0–100) on the AOFAS score. There is no official agreement on the minimal clinical important difference for the AOFAS score regarding ankle OA. However in relatable musculoskeletal literature, 10%–15% of the used scale was reported.^13 25 26^ Our predefined minimal clinical important difference of 12% is located within this range.^13 25 26^ Based on a previous placebo-controlled RCT on injection therapy (hyaluronic acid) in ankle OA by De Groot *et al*, an SD of 16.3 can be expected.^6^ Taking into account a two-sided level of significance of 5%, a power of 90% and a dropout rate of 10%, approximately 50 (45 plus 10% drop out) patients per group will be needed (n=100 in total).

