### Primary outcome measure

Analysis will be performed using an intention-to-treat approach. To test for the effect of treatment on the between-group difference in primary outcome, we will use a repeated measurement general linear model. Changes from baseline to all follow-up time points will be included in the model. Adjustments will be made for those baseline variables that influenced the primary outcome with p<0.10.

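### The primary model's covariates are picked by p<0.10 against the trial's own outcome, so the model is not fixed in advance; the distortion is modest and its form depends on a screen the protocol does not describe

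*Protocol article*

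**What the plan says.** In the Statistical analysis part, under Primary outcome measure, the protocol article sets out the analysis population ("Analysis will be performed using an intention-to-treat approach"), the model ("we will use a repeated measurement general linear model. Changes from baseline to all follow-up time points will be included in the model") and the rule for covariates: "Adjustments will be made for those baseline variables that influenced the primary outcome with p<0.10". The section on secondary outcomes uses the same model without a selection rule, so the rule applies to the confirmatory analysis only.

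The article names no covariate and no candidate list. It does not say whether variables are screened singly or jointly, or whether treatment is in the screening model.

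The section on randomisation describes a "computer-generated block randomisation scheme with patients stratified to centre". The analysis section does not mention centre. Table 1 shows that AOFAS is collected at baseline.

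**The concern.** A primary analysis should be determined before the outcome data are seen. Here the threshold is fixed but the model is not: which variables enter depends on how they happen to correlate with AOFAS in this sample. Two consequences follow.

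- **Inference.** The final model is fitted as if its covariates had been given beforehand. The step that chose them is not reflected in the estimate, the standard error or the p-value.
- **Which variables enter.** A design factor such as centre should be in the model because the randomisation used it, not because it reached a p-value. A moderate prognostic factor is kept or lost largely by chance.

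This goes beyond a detail left to the analysis plan. The rule is stated in the protocol, and an analysis plan that followed it would carry the problem forward.

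**Working it through.** **Inputs from the article.** Effect: "designed to detect a difference of 12 points (0–100) on the AOFAS score". Variability: "an SD of 16.3 can be expected". Two-sided 5% level, 90% power, 10% dropout, 45 evaluable and 50 randomised per group.

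**The plan's own figure first.** n per group = 2(1.960 + 1.282)² × 16.3²/12² = 2 × 10.51 × 1.845 = 38.8, so 39, or 40 with the t-test. Dividing 40 by 0.9 gives 44.4, so 45 per group including dropout. The article gives 45 before dropout and 50 after, so its figure is not reproduced. The difference is conservative: 45 evaluable per group gives about 93–94% power. It matters here only as a cushion.

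**Why the screen matters.** Adjusting for a covariate changes the treatment estimate by (slope × chance imbalance).
- *Treatment left out of the screen.* When treatment works, a variable out of balance by chance correlates with outcome partly through treatment. Variables whose imbalance runs with the effect are picked more often, and adjusting for them removes some of the effect.
- *Treatment in the screen.* Selection depends on the within-group association only, which is unrelated to the imbalance. The estimate stays centred. But the selected slopes are those that looked large, so the residual variance, and with it the standard error, comes out too small.

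**Simulation 1.** 45 per group, SD 16.3, one time point, ordinary least squares, 6,000 runs per setting. Assumed: 5, 10 or 20 candidates, either all unrelated to outcome or including two prognostic ones (r = 0.4 and 0.3). The fixed set adjusts for all candidates. Monte Carlo error is about 0.04–0.05 points for a mean and √(0.05 × 0.95/6000) = 0.3 percentage points for a type I error.

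| Candidates | Mean estimate (true 12): fixed set / screen without treatment / screen with treatment | Type I error, %: same order |
|---|---|---|
| 5, none prognostic | 11.97 / 11.77 / 11.97 | 4.9 / 5.2 / 5.6 |
| 10, none prognostic | 11.97 / 11.58 / 11.99 | 5.0 / 4.9 / 5.8 |
| 20, none prognostic | 11.99 / 11.22 / 11.99 | 5.2 / 5.3 / 7.1 |
| 10, two prognostic | 11.92 / 11.62 / 11.92 | 5.0 / 4.8 / 5.3 |
| 20, two prognostic | 11.95 / 11.35 / 11.96 | 4.4 / 4.7 / 5.9 |

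With 20 unrelated candidates and treatment in the screen, the model standard error under no effect is 3.34 against an empirical 3.59 (3.34/3.59 = 0.93), and coverage is about 93%. The lowest power under either form of selection is 90.5%, with 20 unrelated candidates and treatment left out.

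**Simulation 2.** Same size and SD; baseline AOFAS (assumed correlation 0.5 with follow-up) plus unrelated candidates, 4,000 runs per setting.
- Treatment left out: mean estimate 11.9, 11.8, 11.5 and 11.3 with 5, 10, 15 and 25 candidates; type I error near 5%.
- Treatment in, 25 candidates: no shrinkage; standard error 2.93 against an empirical 3.12; type I error 6.4%, against 5.2% for fixed baseline adjustment.
- Power stays above 96%.

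**Chance of passing the screen** (Fisher z, n = 90, critical value 1.645).
- A factor with r = 0.2: atanh(0.2) × √87 = 0.203 × 9.33 = 1.89; Φ(1.89 − 1.645) ≈ 0.60.
- Baseline AOFAS against change, about r = −0.47 with the 12-point effect present: 0.510 × 9.33 = 4.76; Φ(4.76 − 1.645) ≈ 0.999.

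**The case against.** The strongest reply is that the rule and its threshold are declared beforehand, that the primary analysis and its interpretation are completed before unblinding (Study design; Randomisation, blinding and treatment allocation; Statistical analysis), and that the numerical harm is small. Much of this stands. The blinded interpretation limits steering toward a named arm. It does not fix the covariate set, and it does not remove the shrinkage or the understated standard error, which arise mechanically.

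It is also fair to say that an article may leave a candidate list, or the pooling of small centres, to a fuller document. Their absence is not the point here. If the full plan adds centre regardless of its p-value, that part of the concern falls away; the selection rule remains.

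A reader might infer more than the article supports:
- *That selection necessarily biases the estimate toward no effect.* This holds only if treatment is left out of the screen, which the article does not say.
- *That the false-positive rate reaches 7–8% because the significant one of an adjusted and an unadjusted result could be reported.* The article plans one adjusted analysis and no such choice.
- *That baseline AOFAS may be dropped.* At the assumed correlation of 0.5 it passes about 99.9% of the time. The point bears on centre and on moderate prognostic factors.

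**Conclusion.** The concern holds in a limited form: the primary model is chosen from the outcome data and is not fixed in advance, and the direction of the resulting distortion cannot be read from the article. Across the settings run it is either a loss of about 0.1 to 0.8 points of 12 (at most 0.78/12 = 6.5%) with type I error near 5%, or an unbiased estimate with an understated standard error and a type I error of about 6–7% when candidates are many. With five candidates either effect is slight.

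The sizes rest on assumed numbers and strengths of candidates and on a single time point in place of the repeated-measures model. The case for change rests mainly on the unfixed confirmatory model rather than on the size of the bias. Grade: should fix.

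**What to change.** Replace the selection sentence under Primary outcome measure with:

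> *The primary model adjusts for baseline AOFAS and centre (small centres pooled before unblinding), fixed in advance. No covariate is selected on its p-value. Other prognostic variables, named before database lock, are used only in a sensitivity analysis.*

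Both variables are already available: centre from the randomisation, baseline AOFAS from Table 1. The cost is one sentence and a few degrees of freedom for centre; the article does not give the number of centres. The fixed list should stay short: in simulation 1, adjusting for all 20 unrelated candidates brought power down to about 85%.

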### Secondary outcome measures

To test for the effect of treatment on between-group differences in secondary outcomes, we will use the repeated measurement general linear model. Changes from baseline to all follow-up time points will be included in the model.

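### Baseline value and centre are not fixed terms in the change-from-baseline models, which costs precision on the secondary outcomes, and the same model does not suit four-category satisfaction

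*Protocol article*

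**What the plan says.** All references are to the protocol article.

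- **Randomisation, blinding and treatment allocation:** a "computer-generated block randomisation scheme with patients stratified to centre", with variable blocks of 2, 4 or 6.
- **Primary outcome measure (statistical analysis):** a repeated-measures general linear model with change from baseline at every follow-up time as the response. Covariates are the baseline variables found to influence the primary outcome at p<0.10. Neither baseline AOFAS nor centre is named, and the candidates for the screen are not listed.
- **Secondary outcome measures (statistical analysis):** "To test for the effect of treatment on between-group differences in secondary outcomes, we will use the repeated measurement general linear model", again on changes from baseline. No covariate is stated and no outcome is excepted.
- **Secondary study parameters/end points:** the list includes patient satisfaction in four categories from poor to excellent.
- **Inclusion, note to Table 1:** the questionnaires are FAOS, AOS, VAS, AAS, SF-36, GAS and EQ-5D-3L. Satisfaction is not listed as a separate item. The abbreviation key runs it together with SF-36, whereas the end-point list keeps the two apart.
- **Sample size:** the trial is "designed to detect a difference of 12 points (0–100) on the AOFAS score", and "an SD of 16.3 can be expected". The text does not say whether this is the SD of a score or of a change.

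**The concern.** An unadjusted change score forces the slope on baseline to be 1. Baseline adjustment (ANCOVA) estimates the slope and, apart from the degree of freedom it uses, is never less precise. Stratifying by centre and then omitting centre leaves between-centre variation in the residual, so the reported standard error is too large if centres differ. Both variables will be available for every patient, so this precision costs nothing to recover.

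The article makes these choices in its text: the form of the response, the covariate rule for the primary outcome, and one model for all secondary outcomes. The effects at stake are wider intervals for the continuous secondary outcomes, covariates in the primary model that depend on the observed data, and a model that does not fit one listed end point.

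**Working it through.** **1. The plan's own figure.** Inputs from Sample size: difference 12, SD 16.3, "two-sided level of significance of 5"%, and "a power of 90% and a dropout rate of 10"%.

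n per group = 2(1.960 + 1.282)² × 16.3² / 12² = 38.8, so 39 (40 with the t distribution). The article gives "approximately 50 (45 plus 10% drop out) patients per group will be needed (n=100 in total"). The step from 45 to 50 reproduces (45/0.9 = 50), but 45 does not follow from the stated inputs. The difference is on the conservative side: 45 per group gives 93.7% power (normal) or 93.2% (t). This is separate from the present point and matters here only because it leaves some margin.

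**2. Baseline value.** Let s0 and s1 be the baseline and follow-up SDs and r their correlation, which the article does not give. Residual variance per patient:

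- change score: s0² + s1² − 2r·s0·s1
- baseline-adjusted: s1²(1 − r²)
- difference: (s0 − r·s1)², which is never negative

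With s0 = s1 the ratio is 2(1 − r)/(1 − r²) = 2/(1 + r).

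| assumed r | variance ratio | interval width ratio (square root) | equivalent loss of patients, 1 − (1+r)/2 |
|---|---|---|---|
| 0.3 | 1.54 | 1.24 | 35% |
| 0.5 | 1.33 | 1.15 | 25% |
| 0.7 | 1.18 | 1.08 | 15% |

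This applies to each continuous secondary outcome if it is analysed as the article states. Under randomisation both analyses are unbiased.

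**3. Would the primary screen admit baseline AOFAS?** With equal SDs the correlation between change and baseline is −√((1 − r)/2): −0.59, −0.50 and −0.39 at r = 0.3, 0.5 and 0.7. Simulation used 45 per arm, a 12-point effect, SD 16.3, 3,000 runs per setting, and a screen that allows for treatment group. Baseline AOFAS passes p<0.10 against the change score in 100%, 100% and 99% of trials. Against the 26-week score it passes in 89%, 100% and 100%. So, if it is screened at all, it nearly always enters.

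**4. Centre.** Neither the number of centres nor the between-centre share of variance (ICC) is given. If allocation is perfectly balanced within centre, the SE without centre is too wide by a factor 1/√(1 − ICC): 1.026 at ICC 0.05 and 1.054 at 0.10. A simulation with blocks of 2, 4 or 6, assuming six centres of 15 patients, gave:

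| assumed ICC | mean SE without centre | mean SE with centre | excess |
|---|---|---|---|
| 0.05 | 3.41 | 3.35 | about 2% |
| 0.10 | 3.40 | 3.26 | about 4% |

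At ICC 0 there is no cost. Type I error without centre at ICC 0.10 was about 4.0%, below the nominal 5%.

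**5. Satisfaction.** No arithmetic is needed. The stated model takes a numeric change from baseline. The outcome is a set of four ordered categories, and the note to Table 1 shows no baseline measurement of it from which a change could be formed.

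**The case against.** **A reader might infer that the trial falls short of its 90% power.** With 16.3 read as a score SD, r = 0.3 and no baseline term, 45 per group gives 83.9% for a change score against 95.6% with adjustment. The documents do not support that conclusion. These are the sizing inputs of the primary outcome, whose model is not unadjusted: step 3 shows that its rule would usually bring baseline AOFAS in. The shortfall also needs r of about 0.4 or less (89.0% at 0.4, 93.7% at 0.5). If 16.3 is the SD of a change, power is 93.7% even without adjustment. No secondary outcome has a stated power.

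**A reader might infer that baseline data are collected and then ignored.** They are not. A change score uses the baseline, only inefficiently, and the primary model also draws on baseline variables.

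**An article may leave covariates to the analysis plan.** This is the strongest objection, and it holds for details such as how small centres are pooled. It does not remove the point, because the article itself fixes change scores, a p-value screen and a single model for all secondary outcomes. It gives a covariate rule for the primary outcome and none for the secondary ones. An unseen plan may nevertheless add the terms.

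**Centre is minor.** This stands: the effect is small, conservative, and rests on an assumed ICC.

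**Satisfaction could be scored 0 to 3 and put in a linear model.** This also stands in part, so it would be too strong to say that the analysis cannot be carried out. The absence of a baseline is inferred from the Table 1 note and is not stated outright. What remains is that the model is a poor match for the outcome.

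**Conclusion.** The point holds as a matter of precision and pre-specification, not of bias or inflated type I error.

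- **Continuous secondary outcomes:** variance is 18% to 54% larger than needed for r from 0.7 down to 0.3, assuming equal SDs and no covariate beyond what the article states. This is the main part.
- **Primary outcome:** the gain is mainly that baseline AOFAS and centre would be settled in advance instead of by the observed p-values. No loss of the planned power is demonstrated.
- **Centre:** the SE is about 2% to 5% too wide at an assumed ICC of 0.05 to 0.10, with no cost at ICC 0.
- **Satisfaction:** a linear change-from-baseline model does not suit a four-category ordinal item with no baseline shown.

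The correlation, the ICC and the number of centres are assumptions. The direction of the baseline result does not depend on them, since in large samples adjustment is never less precise.

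**What to change.** In the primary model and every continuous secondary model, name that outcome's baseline value (with a baseline-by-visit interaction) and centre as fixed terms, whatever their p-values. State the rule for pooling small centres and apply it before unblinding. Analyse satisfaction as the category reported at follow-up, with a proportional-odds model adjusted for centre and no change score.

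This changes wording only. The variables are already collected, and neither the design nor the sample size is affected. The cost is a few degrees of freedom, mostly for centre.

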### Economic analysis

In the event of a positive significant outcome, an economic analysis is needed to support a possible change of practice. An economic analysis (costs) will be performed in order to determine cost-effectiveness.

We will assess the differences in mean quality-adjusted life years (QALYs), costs and net benefits between the PRP injection group and the placebo group using linear models. We express the cost-effectiveness by using cost-effectiveness acceptability curves from both a healthcare perspective and a societal perspective. With multiple bootstrap replicates of the average difference in costs and effects in the incremental cost-effectiveness plane, we will express the uncertainty of our cost-effectiveness analysis.

The cost-effectivity analysis will be performed with a 1 year time horizon. We use the three-level EQ-5D questionnaire (Euroqol, Rotterdam, the Netherlands) to calculate QALYs as the area under the curve of the utility scores measured over 12 months, according to the Dutch pricing system. The analysis will be based on indirect costs and direct costs and will be determined using PRODISQ. PRODISQ is taken at baseline and every 3 months thereafter up until 1 year.

### Monitoring committee

The PRIMA trial will be monitored by the clinical research unit (CRU) of the coordination study centre. The CRU aims to improve the quality of clinical research and ultimately, patient care. Before the PRIMA trial commenced, a monitoring plan was set-up. This monitoring plan facilitates compliance with the Human Research Act (WMO), GCP (ICH-GCP) guidelines (5.18.1) and/ or ISO14155, which require monitors to verify that:

the rights and well-being of human subjects are protected;recorded study data are accurate, complete and verifiable with the source documents;the conduct of the study is compliant with the currently approved protocol and with applicable laws regulatory requirements, for example, WMO, ICH-GCP, ISO14155.

Throughout the study, monitoring will be performed at initiation of the trial, at each participating centre once approximately three patients have been enrolled, after approximately 10–15 enrolled patients have completed the 26-week follow-up, after 70 patients have been enrolled and after database lock.

### Ethics and dissemination

In the events of amendments or other changes, co-researchers will be notified. If relevant, patients participating will also be notified. Intellectual data will be the property of the PRIMA study group. Participant data that underline the results reported in this article following de-identification will be shared anonymously on request following publication. Data will be shared, wherever legally and ethically possible and in line with ICMJE guidelines, with researchers who provide a methodologically sound proposal. Data will be stored in a repository (Figshare) under management of the medical library of the AMC. Any proposal should contain: title, background, rationale, objective, methods (eligibility criteria, variables and timeframe of interest, statistical plan), information regarding publication including authorship.

The results of this project study and new knowledge will be disseminated through the Dutch Arthritis Association (ReumaNederland), presentations, news publications, blogs, websites, social media and professional organisations (rheumatology, orthopaedics, primary care medicine, sports medicine, public health) and the Dutch patient federation (Patiëntenfederatie Nederland). The patients will also be informed about the results of the study. The study will be conducted according to the principles of the Declaration of Helsinki, GCP and the Medical Research Involving Human Subjects Act (WMO). The board of each participating hospital reviewed and approved the local feasibility. Monitoring and auditing will be carried out throughout the study. In the event of serious adverse events, these will be documented and reported to the monitor and the Medical Ethics board. Eligible patients will be informed of the study and will sign an informed consent form before participating (acquired by researchers associated with the study). Provisions for post-trial care as compensation for those who suffer harm from trial participation is documented in the patient information.

